#### 2.5.4 Primary and Secondary Outcomes

The primary outcome for the effectiveness trial will be child lifestyle pattern score ‘Discretionary food and screen time’ at 18 months. This is a composite measure of child diet, physical activity and screen time derived from a previous analysis (44) of the INFANT RCT (13) and INFANT Extend RCT (33) using principal component analysis. This has been selected as the primary outcome based on previous research (44) confirming the early clustering of these behaviours into unhealthy versus healthy lifestyle patterns in children as young as 18 months of age. Further, these lifestyle patterns track from early childhood into later childhood and adulthood, and are associated with overweight and obesity (45).

Secondary outcomes of the effectiveness trial will include (i) proportion of mothers with any breastfeeding at 12 months; (ii) energy-balance behaviours including child diet (fruit, vegetables, non-core drinks and snacks), child time physically active and sedentary, scores on the ‘Fruit, vegetables and outdoor time’ lifestyle pattern (12 & 18 months), and scores on the ‘Discretionary food and screen time’ lifestyle pattern (12 months) (44); (iii) infant BMIz at 12 months and 18 months, and (iv) child classification as overweight or obese according to WHO definitions (46).

#### 2.5.5 Sample Size

The trial aims to recruit 1,500 primary carer/infant dyads in each arm (total 3,000). Assuming a conservative attrition rate of 33%, it is expected that complete data on 2,000 primary carer/infant dyads (1,000/arm) will be collected. The statistical software PASS version 14.0.9 (NCSS, LLC) was used for all power calculations, assuming that 190 first-time parent groups will run in each arm with an average number of 5.4 children with complete data per group and a coefficient of variability in group size of 0.32, as observed in the INFANT RCT (13) (α=0.05; two-sided tests). A target sample size of 1,000 infants per arm achieves 80% power to detect a mean difference between arms of at least 0.17 points in the lifestyle score ‘Discretionary food and screen time’ at 18 months [primary outcome; standard deviation within clusters (SD) =1.21, intracluster correlation coefficient (ICC) = 0.048]. In our former INFANT trial (44) the difference in “Discretionary food and screen time” pattern score was 0.29 (95% CI: 0.08, 0.49).

The target sample size (1,000 infants per arm) also achieves 80% power to detect the following differences in secondary outcomes:

1) 6.2% increase in the proportion of mothers with any breastfeeding at 12 months assuming the proportion in the control group will be 27% (ICC =0.05);2) a mean difference (at 18m) between study arms of a) 0.24 serve/day in fruit [SD=1.7, ICC=0.071]; b) 0.25 serve/day in vegetables [SD=2.0, ICC=0.000]; c) 0.06 serve/day in non-core drinks [SD=0.44, ICC=0.034]; d) 0.06 serve/day in non-core sweet [SD=0.39, ICC=0.064]; e) 0.05 serve/day in non-core savoury [SD=0.33, ICC=0.047]; f) 6.7 min/day of screen use [SD=44, ICC=0.11]; and g) 18.4 min/day of physical activity [SD=143, ICC=0.018]. While individual energy-balance behaviour changes appear small, modest increments in energy consumption (126-189kJ/day (30-45 calories)) are estimated to promote population weight gain over time. Collectively these changes have capacity to influence weight gain trajectories at a population level (47, 48);3) a mean difference between arms of at least 0.13 change in BMIz score by 12 months [SD=1.0, ICC= 0.021]. Assuming a mean BMIz of 0.41, a 0.13 reduction in BMIz to 0.28 equates to a 1.3% reduction in prevalence of overweight and obesity, considered meaningful at a population level.

#### 2.5.6 Data Collection and Analysis

Infant diets will be measured by a validated Food Frequency questionnaire (FFQ) with average percentage categorical agreement against three days of 24 hour recall of 62-64% (49). Infant physical activity will be measured using a single parent-reported question with good test-retest reliability (ICC 0.62) (50). Infant screen time will be measured using a single parent-reported question with excellent reliability (ICC 0.84) (51). Change in BMIz measured at 12 and 18 months will be derived from child height and weight which is routinely collected by MCH nurses and will be made available in de-identified form to the research team. These data are typically available for 80% and 71% of infants at 12 and 18 months respectively (52). Lifestyle pattern scores will be calculated as linear combinations of the standardized dietary (fruit, vegetables, water, discretionary sweet foods, discretionary savory foods), outdoor and television viewing items, using the principal component analysis factor loadings previously published from the combined INFANT and INFANT Extend datasets (44).

Covariates will include self-reported parent socio-demographic characteristics (including marital status, education level, age, sex, Indigenous status, language spoken at home, country of birth, years lived in Australia, health care card holder) parent weight and height, pre-pregnancy weight, self-rated coping, sleep and health, infant sex, birth weight and temperament. Baseline characteristics will be compared between arms using linear mixed models (LMM) or generalized estimating equations (GEE) with link and distribution selected based on the type of variable. The effect of the intervention on the primary outcome (‘Discretionary food and screen time’ lifestyle pattern) will be estimated using a LMM including arm, time (12 and 18 months), interaction arm-time and any baseline variable showing clear imbalance between arms (covariates) as fixed effects. The same LMM model will be used for numerical secondary outcomes. All mixed models will include MCH group as a random effect to account for clustering. The effect of the intervention on proportion of mothers with any breastfeeding at 12 months will be estimated using a GEE model with logit link and binary distribution including arm, time (12 and 18 months), interaction arm-time and baseline confounders. If appropriate, multiple imputation will be used to handle missing data.

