## 1 Introduction

The prevention of obesity in early life is a key priority identified by the World Health Organization (1). The dietary and activity (energy-balance) behaviours associated with overweight and obesity begin in and track from early childhood (2). In Australia, a minority of children meet dietary, physical activity or sedentary behaviour guidelines (3). Children experiencing rapid weight gain during the first two years of life are also nearly four times more likely to become overweight or obese later in life (4). Globally, an estimated 41 million children aged under five are affected by overweight or obesity (5), including nearly one quarter of Australian children aged 2-4 years (3). Addressing energy balance behaviours in early life is therefore critical (6).

The prevalence of overweight and obesity, and the energy balance behaviours that predict them, are culturally, geographically and socioeconomically patterned (7–9) such that the most disadvantaged are disproportionately affected (8). It is estimated that obesity and dietary risks are each responsible for approximately 15% of the gap in disease burden between Aboriginal and Torres Strait Islander peoples and non-Indigenous Australians (10). Preventive interventions must therefore reach families across social, cultural and geographic divides. Most population-based interventions to improve children’s health behaviours in early life occur *via* settings, such as child care. These do not reach most children in their first year of life, where the risks for later overweight and obesity begin. At this time, the main influences on children’s health behaviours are the family and home environment (11) with a key avenue for reaching parents through Maternal and Child Health (MCH) services.

In Australia, routine universal MCH services are provided in all Australian states and territories. In Victoria, Australia, this service includes 10 free ‘key age and stage’ consultations with a MCH nurse (nine occurring between birth and two years of age) with a strong focus on promoting optimal child development and growth (12). More than 95% of Victorian parents attend these consultations between birth and four months, with over 80% still attending at 12 months (12). Routine preventive care services, such as those provided through MCH services, therefore offer a circumscribed opportunity to support parents in the establishment of healthy behaviours during infancy and early childhood.

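### BMIz is listed as a level at 12 and 18 months but called a change, with no baseline named, in the sample size and analysis text; the plan's own figures fit the level

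*Protocol article*

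**What the plan says.** Section 2.5.4 of the protocol article lists the secondary outcome as "iii) infant BMIz at 12 months and 18 months". Table 2 gives the same two ages and no earlier one for BMIz.

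Section 2.5.5 powers "a mean difference between arms of at least 0.13 change in BMIz score by 12 months [SD=1.0, ICC= 0.021" and then illustrates it: "Assuming a mean BMIz of 0.41, a 0.13 reduction in BMIz to 0.28 equates to a 1.3% reduction in prevalence of overweight and obesity".

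Section 2.5.6 says "Change in BMIz measured at 12 and 18 months will be derived from child height and weight which is routinely collected by MCH nurses". The linear mixed model described there has arm, time (12 and 18 months) and their interaction, and the same model serves all numerical secondary outcomes. Birth weight and infant sex are on the covariate list, but a baseline variable enters the model only if it is clearly imbalanced between arms. BMIz at or before three months is not on the list.

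Section 2.5.7 takes the between-arm difference in BMIz into the lifetable model.

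**The concern.** A level and a change are different quantities with different standard deviations, and a change needs a stated starting point. None is given. From the ages at which BMIz is listed, the only change that can be computed is from 12 to 18 months. That does not match a change *by* 12 months, and it would subtract out any intervention effect already present at 12 months, the age that Table 1 labels post-intervention. An analyst who follows section 2.5.6 literally could therefore report something other than the outcome in section 2.5.4, and carry it into the cost-effectiveness result.

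A second issue concerns the same model. The arms are non-randomised and recruited one after the other, so body size at birth may differ between them. A rule that admits birth weight only on visible imbalance takes no account of how strongly it predicts BMIz. A moderate imbalance in a prognostic variable can be passed over and left as confounding.

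**Working it through.** **Inputs from section 2.5.5.** Difference 0.13; SD 1.0; ICC 0.021; "α=0.05; two-sided tests"; 1,000 infants per arm for 80% power; 190 groups per arm with 5.4 children each (190 × 5.4 = 1,026); coefficient of variation of group size 0.32.

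**Step 1: reproduce the stated power, with SD 1.0 as the SD of the outcome analysed.**
- Design effect = 1 + ((1 + 0.32²) × 5.4 − 1) × 0.021 = 1 + (5.953 − 1) × 0.021 = 1.104.
- n = 1,000: SE = √(2 × 1.104 / 1,000) = 0.0470. Power = Φ(0.13/0.0470 − 1.96) = 79.0%; detectable difference at 80% power = 0.132.
- n = 1,026: SE = √(2 × 1.104 / 1,026) = 0.0464. Power = 80.0%; detectable difference = 0.130.
- Reading SD 1.0 as within-cluster gives 78.2% and 79.2%.

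The stated figure reproduces. This step alone does not separate a level from a change whose own SD happens to be 1.0. Step 2 does.

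**Step 2: reproduce the prevalence example.** Take BMIz as normal with SD 1.0 and a cut-off of 2. The cut-off is an assumption, since the text gives no number.
- Mean 0.41: P(BMIz > 2) = 1 − Φ(1.59) = 5.59%.
- Mean 0.28: P(BMIz > 2) = 1 − Φ(1.72) = 4.27%.
- Difference = 1.32 points, matching the stated 1.3%. A cut-off of 1 would give 4.18 points.

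The example uses the same 0.13 with means of 0.41 and 0.28, and gives the share of children above a threshold. It makes sense only for BMIz as a level with SD 1.0. A mixed model with rows at 12 and 18 months also fits a level.

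**Step 3: what a change score would do.** Assume SD 1.0 at both times, correlation r between them, and the same design effect. Then SD of change = √(2(1 − r)). The documents give no r, so all values are assumptions. With n = 1,000 per arm and difference 0.13:

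| r | SD of change | Power | N per arm for 80% |
|---|---|---|---|
| 0.2 | 1.265 | 59% | 1,641 |
| 0.3 | 1.183 | 65% | 1,436 |
| 0.4 | 1.095 | 71% | 1,231 |
| 0.5 | 1.000 | 79% | 1,026 |
| 0.6 | 0.894 | 87% | 821 |
| 0.7 | 0.775 | 95% | 616 |
| 0.8 | 0.632 | 99% | 411 |

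The break-even is r = 0.5, where the SD of change equals the SD of the level.

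**Step 4: what a fixed covariate does to the level.** A baseline covariate with correlation r with the outcome leaves a residual SD of √(1 − r²). At n = 1,000, power rises from 79% to 81%, 83% and 86% for r = 0.2, 0.3 and 0.4 (assumed). The correlation of birth weight with later BMIz is not in the documents, so these values only illustrate the formula.

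**The case against.** The best reply is that the article uses *change* loosely for a between-arm effect. Section 2.5.5 describes between-arm differences in diet and activity as behaviour changes, and section 2.5.7 does the same for the BMIz difference. The 0.13 is followed at once by an example in levels, and the model has no baseline row. On this reading nobody plans a change score and only the wording is at fault. Most of that stands, and it is why the repair is to keep the level. It does not remove the contradiction: section 2.5.6 describes how the outcome will be derived, and there the word is an instruction. An unseen analysis plan may settle the matter, but this document states two definitions.

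It can also be said that early size is not ignored, since birth weight, infant sex, pre-pregnancy weight, and parent weight and height are all candidate covariates. That is correct. The criticism is confined to the rule by which they enter.

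A reader might go further and infer that BMIz at or before three months must be a covariate. The documents do not support that as a requirement. The Introduction describes nurse visits, "nine occurring between birth and two years of age) with a strong focus on promoting optimal child development and growth", which makes early measurements plausible, but nothing says they will be supplied to the researchers; section 2.5.6 gives availability at 12 and 18 months only. The app is also offered from birth, so a measurement at three months may follow exposure, and adjusting for it could remove part of the effect. Nor is a change score always worse than baseline adjustment in non-randomised arms: each is unbiased under different assumptions.

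**Conclusion.** The inconsistency is real: a level in section 2.5.4 and Table 2, a change without a baseline in sections 2.5.5 and 2.5.6. Taken together, the power figure, the prevalence example and the mixed model fit BMIz as a level.

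A reader might infer that the stated 80% power is wrong. It is not shown to be: for the level it reproduces at 79% to 80%. A shortfall arises only if a change is analysed and the correlation is below about 0.5; above that, power exceeds the stated value. These figures assume equal SDs of 1.0 at both times and an unchanged ICC.

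The covariate point is narrower. In non-randomised arms, leaving birth weight to an imbalance rule risks omitting a prognostic confounder. The gain in precision from fixing it is probably modest and cannot be sized from the documents. Infant sex may add little, since Table 2 already lists it among the data for BMIz.

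BMIz is a secondary outcome, so power for the primary outcome is unaffected. The point matters mainly because the BMIz difference drives the economic model.

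**What to change.** 1. In sections 2.5.5 and 2.5.6, define the outcome as BMIz level at 12 and 18 months, as in section 2.5.4 and Table 2, and delete *change*.
2. In section 2.5.7, state that the adjusted between-arm difference in BMIz level is what enters the economic model.
3. In the BMIz model, enter birth weight and infant sex as fixed covariates whatever their observed balance.
4. Optionally add early BMIz in a sensitivity analysis, if the MCH extract supplies it and it predates contact with the app or sessions.
5. If a change score is truly intended, name its baseline measurement and restate the power with the SD of that change.

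The cost is a few words, two extra model terms, and imputation of a few missing birth weights. No additional data collection is needed for items 1 to 3.

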### 2.5 Effectiveness Trial

#### 2.5.1 Trial Design

An embedded non-randomised controlled trial will assess the effectiveness and cost-effectiveness of INFANT when delivered at scale. The trial will involve comparing primary and secondary effectiveness outcomes between a group of INFANT participants (intervention arm) and a non-randomised comparison group recruited within the same communities prior to the implementation of INFANT (usual care arm). This approach enables comparison of outcomes between parents and infants exposed and not exposed to the intervention living in the same geographical areas and therefore sharing socio-demographic characteristics and having access to the same health services. The risk of bias will be reduced by replicating strategies for recruitment, follow-up and assessment in both trial arms and adjusting for unbalanced baseline characteristics. This trial design was deemed appropriate for assessing the effect of INFANT when implemented at scale in real-world conditions, enabling natural dissemination and uptake to be captured. A cluster randomized design with communities allocated to intervention or usual care was deemed not feasible because the prospect of being randomised to the control arm is likely to reduce participation. Within communities, the prospect of parent groups being randomised to a control arm is unethical (given the known efficacy of the intervention) and contamination between groups would be unavoidable. A stepped-wedge cluster randomised study design (43) was also considered but ruled out as randomisation of LGAs to an implementation time period may interfere with natural uptake under real world conditions.

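### The primary mixed model gives each adjustment covariate one coefficient for both ages, so the 18-month contrast is only partly adjusted for any confounder whose effect differs between 12 and 18 months

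*Protocol article*

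**What the plan says.** Section 2.5.4 fixes a single age for the primary analysis: "The primary outcome for the effectiveness trial will be child lifestyle pattern score ‘Discretionary food and screen time’ at 18 months".

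Section 2.5.6 estimates the effect from a linear mixed model on the 12- and 18-month scores. Its fixed effects are "arm, time (12 and 18 months), interaction arm-time and any baseline variable showing clear imbalance between arms (covariates) as fixed effects". Arm by time is the only interaction named. On clustering, the section says: "All mixed models will include MCH group as a random effect to account for clustering". It then extends the specification: "The same LMM model will be used for numerical secondary outcomes".

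Allocation is not randomised. Section 2.5.1 counts "adjusting for unbalanced baseline characteristics" among the ways to reduce bias, and the Discussion repeats it. The other measures named there concern recruitment, follow-up and assessment, so this is the one that belongs to the analysis.

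**The concern.** The model is flexible in one place and rigid in another. The arm difference may change between 12 and 18 months, but the effect of, say, parental education is held equal at both ages. The fitted covariate coefficient is then a compromise between the two. Whatever it fails to remove at 18 months has only one place to go, the arm-by-time term, and that term is part of the primary estimate.

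In a randomised trial the expected imbalance is zero and this would hardly matter. Here a covariate enters the model because it is clearly imbalanced, so every adjusted variable has a non-trivial arm difference. Imbalance is also plausible from the design. Enrolment in the group sessions is opt-in (Section 2.2). The comparison arm is recruited earlier, over 6 months against two years, and may be topped up from other local government areas (Section 2.5.3). A residual at 18 months would look like an intervention effect, or would mask one.

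**Working it through.** **Inputs from Section 2.5.5.** 1,000 children per arm, 80% power, difference 0.17, SD 1.21, ICC 0.048, mean group size 5.4, coefficient of variation of group size 0.32, "α=0.05; two-sided tests". The arm imbalances and age-specific covariate effects are not in the protocol; all values used for them below are assumptions.

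**The plan's own figure.** Design effect = 1 + ((0.32² + 1) × 5.4 − 1) × 0.048 = 1.2377. Taking 1.21 as the total SD, 796 per arm without clustering × 1.2377 gives 986, and power at 1,000 is 80.6%. Taking 1.21 as the within-group SD (total 1.240) gives 1,035 per arm, against 190 × 5.4 = 1,026 with 79.7% power. The sample size reproduces and is not in question. The standard error of the 18-month contrast is 1.21 × √(2 × 1.2377/1000) = 0.0602.

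**Algebra.** Let d be the arm difference in a confounder (in SD), and b12 and b18 its effect per SD at each age. Arm, time and arm by time together saturate the four cell means, so the covariate coefficient is estimated within cells. With equal variances and equal numbers at both ages it estimates (b12 + b18)/2. Then:

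- unadjusted bias at 18 months = d × b18
- removed by the model = d × (b12 + b18)/2
- residual at 18 months = d × (b18 − b12)/2
- residual at 12 months = −d × (b18 − b12)/2

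**Size over an assumed range.** Residual in points for one confounder:

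| d (SD) | change 0.05 | change 0.1 | change 0.2 | change 0.3 |
|---|---|---|---|---|
| 0.1 | 0.0025 | 0.005 | 0.010 | 0.015 |
| 0.2 | 0.005 | 0.010 | 0.020 | 0.030 |
| 0.3 | 0.0075 | 0.015 | 0.030 | 0.045 |
| 0.5 | 0.0125 | 0.025 | 0.050 | 0.075 |

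Against 0.17 points, the extremes are 0.0025/0.17 = 1.5% and 0.075/0.17 = 44%. The middle case is 0.030/0.17 = 18%. Two-sided type I error is Φ(−1.96 + bias/SE) + Φ(−1.96 − bias/SE). With SE 0.0602 it is 5.0% at the low end, 7.9% in the middle (0.030/0.0602 = 0.50 SE) and 23.8% at the top.

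**Simulation check.** 190 groups of 5 children per arm, SD 1.21, ICC 0.048, no true effect, 200 runs per scenario, assumed within-child correlation 0.5:

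| d, b12, b18 | Residual by formula | Planned model | With covariate by time | Mean paired difference |
|---|---|---|---|---|
| 0.3, 0.1, 0.3 | 0.030 | 0.032 | 0.003 | 0.0296 |
| 0.3, 0.1, 0.2 | 0.015 | 0.016 | 0.001 | 0.0152 |
| 0.5, 0.1, 0.4 | 0.075 | 0.062 | −0.012 | 0.073 |
| 0.3, 0.2, 0.2 | 0 | 0.004 | 0.004 | −0.0005 |

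The paired difference is the steadier comparison because both models see the same data, and it matches the formula. Adding a child random intercept to the planned model leaves the first row at 0.032. Empirical standard errors were 0.067 (planned) and 0.068 (extended) in the first row, and 0.063 for both in the last.

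**Direction.** If the effect shrinks, the sign turns. With d = 0.3, b12 = 0.3 and b18 = 0.1, the unadjusted bias is 0.03, the model removes 0.3 × 0.2 = 0.06, and −0.03 is left.

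**Unequal numbers.** Fewer 18-month records pull the pooled coefficient towards b12. For BMIz, Section 2.5.6 expects data on 80% and 71% of infants. Ignoring the small clustering effect, the share of the change left at 18 months is about 0.80/(0.80 + 0.71) = 53% rather than 50%.

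**The case against.** The strongest objection is that the premise is not in the document. A reader might infer that discretionary foods and screens are only emerging at 12 months, so that social gradients must be steeper at 18 months and the primary contrast is bound to be under-adjusted. Nothing in the protocol supports that. Section 2.5.4 reports that the behaviours cluster by 18 months and gives no comparison with 12 months. The score is built from standardised items, and the article does not say whether they are standardised within age. If they are, differences in spread between the ages largely drop out. This objection stands: the bias is conditional, and its sign is unknown.

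The magnitudes are also assumed, and recruiting both arms from the same communities with the same procedures is meant to keep imbalance small. That stands too; the lower part of the table is immaterial. A reader might obtain a larger residual by supposing a less variable 12-month score and fitting a within-child covariance. That is not the model described, whose only named random effect is the MCH group.

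Lastly, one coefficient per covariate is a conventional repeated-measures form, the text does not literally exclude further interactions, and an unseen analysis plan may add them. This lowers the grade of the point but does not remove it. The article states a specific list with one interaction, and a better form is available from the same data.

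**Conclusion.** The point holds conditionally, as a nearly free improvement rather than an error in the plan; confidence is moderate. As listed, the model leaves d × (b18 − b12)/2 in the 18-month primary contrast for each adjusted confounder, given equal variances and numbers at both ages. That is zero if the effect is stable, under-adjustment if it grows and over-adjustment if it shrinks. Several confounders acting in the same direction would add up.

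Over the assumed range this is negligible at one end and a material share of the target difference at the other. It reaches the upper end only with a sizeable imbalance and a clear change in effect. The case for acting rests on the design, where adjustment is the analytic safeguard, and on the low cost, not on evidence that such a bias is present.

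**What to change.** In Section 2.5.6, add covariate-by-time terms for every adjustment covariate in the primary mixed model. Alternatively, state that the 18-month contrast will be adjusted with covariate coefficients estimated at 18 months. Apply the same wording to the numerical secondary outcomes that share the model.

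The cost is one extra degree of freedom per covariate parameter: one for a continuous or two-level variable, and more for multi-level variables such as marital status, education or country of birth. With about 2,000 children this is negligible, and the simulations showed no visible loss of precision. No new data are needed and the sample size does not change. Where covariate effects are the same at both ages, the two models agree, so nothing is lost if the concern proves empty.

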**Figure 1 f1:**
[figure not shown]
Evolution of INFANT program from efficacy testing to state wide scale up.

To reflect the move from trial phase to scale up, the acronym INFANT was changed from ‘Infant feeding activity and nutrition trial’ to INfant Feeding, Active play and NuTrition. Health services will be encouraged to offer the app from birth aligned with routine services and through INFANT group sessions starting at 3 months of age. Promotion of the app will be *via* flyers and posters in health services, and SMS and referral during MCH key age and stage consultations. Enrolment of parents to the group sessions will be *via* existing systems for group programs locally. In the original RCT, this involved inviting first time parent groups to continue to meet for INFANT sessions. In the small-scale translation study, areas continued to use this approach, with some making the last session of the first-time parent group (usually when infants were around three months old) the first INFANT session. This opt-in model of enrolment was identified as promoting intervention uptake with parents (26).

Box 1INFANT key messages.

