## 3 Discussion

The evaluation of effective interventions delivered at scale is a crucial, yet under-researched aspect of changing population-level health behaviours and essential to reducing the evidence to practice and policy gap. Examining implementation and effectiveness outcomes concurrently using a hybrid implementation and effectiveness trial design however comes with a number of challenges. Recruitment to the effectiveness trial is contingent on sufficient uptake of INFANT by organisations which in turn is shaped by a wide range of contextual factors outside of the control of the research team. Hence implementation outcomes determine the feasibility of conducting an embedded effectiveness trial within the timeframes of the study. Designing such a trial is also methodologically challenging as traditional trial designs such as RCT, cluster RCTs and stepped-wedge designs, which require organisations to be randomized to control arms, can interfere with the natural uptake of the intervention under ‘real world conditions’. The use of a non-randomized design in this effectiveness trial is therefore not without its limitations but will be minimized by recruiting parents exposed and not exposed to the intervention living in the same communities, replicating strategies for recruitment, follow-up and assessment in both trial arms, and adjusting for unbalanced baseline characteristics.

Successful, sustained implementation is likely due to a combination of factors, including the effectiveness of the intervention and the use of appropriate implementation strategies. An improved understanding of the interrelationship of these factors will therefore enable explicit and transparent decisions regarding intervention adoption, implementation and sustainability. To our knowledge, no obesity prevention interventions in early childhood have been implemented and evaluated at scale under real world conditions. The findings from this study will directly inform future delivery of INFANT in Victoria. It will also provide vital implementation, effectiveness and cost-effectiveness evidence to inform the adoption and sustained implementation of early childhood obesity prevention interventions both in Australia and internationally.

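### In a non-randomised comparison, adjusting only for baseline variables that show clear imbalance can leave out several prognostic variables with modest imbalances in the same direction; a fixed adjustment set would avoid this.

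*Protocol article*

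**What the plan says.** Section 2.5.1 sets INFANT participants against "a non-randomised comparison group recruited within the same communities prior to the implementation of INFANT (usual care arm". Section 2.5.3 gives 6 months of recruitment for the comparison arm and two years for the intervention arm, with a three-month gap between them.

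Section 2.5.6 lists candidate variables: "Covariates will include self-reported parent socio-demographic characteristics (including marital status, education level, age, sex, Indigenous status, language spoken at home" and further items, ending with "self-rated coping, sleep and health, infant sex, birth weight and temperament". It then states "Baseline characteristics will be compared between arms using linear mixed models (LMM) or generalized estimating equations (GEE", and puts into the primary model arm, time, their interaction and "any baseline variable showing clear imbalance between arms (covariates) as fixed effects". Numerical secondary outcomes use the same model. The GEE for breastfeeding refers instead to baseline confounders, which it does not define.

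The imbalance rule is offered twice more as a safeguard for the design: "adjusting for unbalanced baseline characteristics" in section 2.5.1 and "replicating strategies for recruitment, follow-up and assessment in both trial arms, and adjusting for unbalanced baseline characteristics" in the Discussion. No threshold for clear imbalance is given, and no variable is named as always included.

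On timing, section 2.2 says "Health services will be encouraged to offer the app from birth aligned with routine services", and section 2.5.3 places the T1 survey at an infant age of up to 3 months.

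**The concern.** The bias from leaving out a variable is roughly its imbalance between arms times its association with the outcome. A rule that looks only at imbalance can drop a strong predictor with a modest imbalance and keep an imbalanced variable that predicts nothing. The second costs only a little precision; the first leaves confounding that the collected data could have removed. Modest imbalances in the same direction are plausible here: enrolment in INFANT is opt-in, the two recruitment periods differ, comparison recruitment may extend to other local government areas, and socio-demographic factors tend to move together. At stake are the primary estimate and the numerical secondary outcomes, including BMIz, which feeds the modelled economic evaluation in section 2.5.7.

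A smaller, related point is that the rule covers any baseline variable. If some intervention families have the app before they complete T1, then coping, sleep, self-rated health or temperament recorded at T1 could already reflect exposure. The rule has no means of telling such a difference from a confounder.

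**Working it through.** **Inputs from section 2.5.5.** 1,000 children per arm with complete data (1,500 recruited), mean group size m = 5.4, CV of group size 0.32, ICC 0.048, within-cluster SD 1.21, target difference 0.17, two-sided α 0.05.

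**The plan's own figure.**
- Design effect = 1 + ((0.32² + 1) × 5.4 − 1) × 0.048 = 1 + 4.953 × 0.048 = 1.238.
- With 1.21 as total SD: SE = 1.21 × √(2 × 1.238/1000) = 0.0602; power = Φ(0.17/0.0602 − 1.96) = 80.6%.
- With 1.21 as within-cluster SD: total SD = 1.21/√(1 − 0.048) = 1.240, SE = 0.0617, power = 78.7%.
- Attrition: 1,000/0.67 = 1,493, against 1,500 stated.

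The stated 80% and the recruitment target reproduce. The sample size is not in question.

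**Assumptions not in the protocol.** Clear imbalance means p<0.05. Covariates have the same design effect as the outcome (1.24). They are independent of one another, shifted in the same direction, and correlated r with the score. There is no true effect.

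**How large an imbalance goes unflagged.** The limit is 1.96 × √(2 × 1.238/n): 0.098 SD at n = 1,000 per arm and 0.080 SD at n = 1,500. An underlying shift of 0.10 SD is flagged 52% of the time at 1,000 per arm and 69% at 1,500.

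**What the rule leaves behind.** I simulated the rule itself: test each covariate, adjust for those flagged, estimate the arm difference (10,000 runs per row, total SD 1.24, clustering represented by dividing n by the design effect). The 1,500 rows test imbalance on all recruited families and analyse 1,000 per arm.

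| Covariates | Shift (SD) | r | Tested on, per arm | Mean bias (points) | % of 0.17 | Type I error |
|---|---|---|---|---|---|---|
| 1 | 0.10 | 0.3 | 1,000 | 0.012 | 7 | 5.1% |
| 1 | 0.10 | 0.3 | 1,500 | 0.007 | 4 | 5.3% |
| 3 | 0.10 | 0.3 | 1,000 | 0.032 | 19 | 8.6% |
| 3 | 0.10 | 0.3 | 1,500 | 0.019 | 11 | 6.2% |
| 5 | 0.05 | 0.2 | 1,000 | 0.036 | 21 | 8.3% |
| 5 | 0.07 | 0.2 | 1,000 | 0.040 | 24 | 9.5% |
| 5 | 0.05 | 0.2 | 1,500 | 0.032 | 19 | 7.9% |
| 5 | 0.07 | 0.2 | 1,500 | 0.032 | 19 | 8.3% |

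Separate runs of the same scenarios at 1,000 per arm gave 5.4% for one covariate, 8.3% for three, and 8 to 10.5% for five. Adjusting for all the covariates whatever their balance gave bias of about 0.001 or less and type I error of 4.8 to 5.2% in every row.

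**Timing.** App access can begin at birth and group sessions at 3 months; T1 runs to 3 months. App exposure before T1 is therefore possible. Age, education, country of birth, pre-pregnancy weight and birth weight cannot be changed by it.

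**The case against.** **The size is easily overstated.** A reader might assume that a covariate shifted by 0.10 SD with r = 0.3 is always omitted. That gives 0.10 × 0.3 × 1.24 = 0.037 points (22% of 0.17) with type I error near 9%, and for three covariates 0.11 points and about 45%. Those figures do not describe the rule. An observed imbalance of 0.10 SD exceeds the 0.098 limit at 1,000 per arm and would be adjusted for. With an underlying shift of 0.10 SD, all three covariates are missed together only about 0.48³ = 11% of the time, and the bias is then about 0.07. This objection stands, and the table reflects it.

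**The p<0.05 trigger is assumed.** The protocol does not mention significance here, and an analysis plan could supply a threshold. That is fair, but a threshold would not cure the fault: any rule based on imbalance alone ignores prognostic strength. Simulating a cut at a standardised difference of 0.1 gave almost the same bias for the five-covariate cases (0.037 and 0.045).

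**The list of covariates might be a fixed set.** Read alone, the sentence opening the list allows this. The model sentence, section 2.5.1 and the Discussion all restrict adjustment to unbalanced variables.

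**App effects adjusted away.** A reader might infer that the rule will remove part of a real effect. The documents do not support that. Services are only encouraged to offer the app from birth, its messages concern feeding, play and screens, and nothing shows that it changes coping, sleep, health or temperament. Dropping these variables outright could itself leave confounding.

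**Steering the result.** A reader might also infer that the covariates could be picked to move the estimate. The candidate list is published, and selection looks at balance between arms, not at the outcome, so this goes too far. Recruitment from the same communities and replicated procedures also give some protection.

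**Conclusion.** The point holds in a limited form. The protocol fixes a selection rule for its primary model that ignores prognostic strength, and presents it as a mitigation for not randomising. This is a stated rule, so it is not a detail left to an analysis plan. A single sub-threshold covariate has little effect (bias about 0.01, type I error about 5%). Several aligned ones leave a bias of about 0.02 to 0.04 points, or 11 to 24% of the difference the trial is powered for, with type I error of roughly 6 to 10%. These sizes depend on the assumed p<0.05 trigger, the covariate design effect, the correlations and the common direction of the shifts. With opposing shifts or weaker predictors the effect is smaller. That T1 coping, sleep, health and temperament may already reflect the app is a possibility raised by the timing only.

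**What to change.** Replace the imbalance rule in section 2.5.6, and its restatements in section 2.5.1 and the Discussion, with one adjustment set named in advance on subject-matter grounds and entered whatever the observed balance. It should be drawn from variables already collected and settled before app access, for example parent age, education, marital status, country of birth and language, Indigenous status, health care card, pre-pregnancy weight with height, infant sex and birth weight. Use the same set in the linear mixed models and in the breastfeeding GEE, in place of the undefined reference to baseline confounders. Keep the comparison of baseline characteristics as description only.

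Add T1 coping, sleep, self-rated health and temperament in a sensitivity analysis, so that the reader can see whether they matter in either direction. Propensity-score overlap weighting on the same fixed set is an optional further check.

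The cost is a change of wording, about 10 to 15 degrees of freedom in about 2,000 children, and some imputation of missing covariates. No new data are needed and the sample size does not change.
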